Characterize cerebrovascular function, cognitive function, proinflammatory cytokines, and cardiometabolic outcome differences between cancer survivors with and without T2DM. We hypothesize that cancer survivors with T2DM will have (1) poorer measures of middle cerebral artery velocity and cerebrovascular conductance, reactivity, and resistance; (2) lower executive function scores; (3) higher C-reactive protein, interleukin-6, and monocyte chemoattractant protein 1 concentrations; and (4) higher blood pressure and insulin resistance.

### Specific Aim 2

Examine pre- to post-PA program differences for changes in Specific Aim 1’s outcomes between cancer survivors with and without T2DM. We hypothesize that greater pre- to post-PA program improvements in these outcomes will be observed for cancer survivors with T2DM.

### Specific Aim 3

Assess pre- to post-PA program differences for changes in Social Cognitive Theory–based (SCT-based) [58,59] constructs, select psychosocial outcomes, HRQoL, and PA between cancer survivors with and without T2DM. We hypothesize that cancer survivors with and without T2DM will demonstrate pre- to post-PA program improvements in (1**)** SCT-based, PA-related self-efficacy, outcome expectations, enjoyment, social support, and barriers; (2) stress, anxiety, mood, and depressive symptoms, and that cancer survivors with T2DM will have greater improvements than cancer survivors without T2DM; (3) in HRQoL due to greater improvements in physical functioning as well as pain intensity/interference, and (4) overall PA participation due to greater increases in light and moderate PA.

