## Methods

### Study Design and Recruitment

We are conducting a National Institutes of Health Stage 1 trial [60], and we have registered this trial on ClinicalTrials.gov (NCT06725953). Moreover, we used the SPIRIT (Standard Protocol Items: Recommendations for Interventional Trials)-Outcomes Guidelines to guide the construction of this manuscript [61]. We are recruiting individuals within Oklahoma City and the greater state of Oklahoma. Our accrual target is 38 participants to allow our desired number of 30 participants to be achieved when accounting for an anticipated 20% attrition rate [62]. We are conducting rolling recruitment and are recruiting via (1) emailed and posted flyers; (2) digital advertising to local survivorship groups; (3) oncologist referral; and (4) chart reviews/assistance from the Stephenson Cancer Center Clinical Trials Office. Potentially eligible individuals are sent a REDCap-based (Research Electronic Data Capture–based) screening survey, and, whenever possible, we are verifying cancer diagnosis, chemotherapy regimen, and T2DM status via medical records. We are evaluating individuals against stringent eligibility criteria. Specifically, our inclusion criteria are as follows: (1) 18 years or older; (2) ability to speak/read English; (3) ability to provide informed consent; (4) underwent treatment within the last 3 years for a non–brain-related cancer with said treatment having included chemotherapy and not currently undergoing any active cancer treatments (ongoing endocrine/hormonal therapy or immunotherapy, when either are used for maintenance purposes, are acceptable); (5) self-reported cognitive difficulties following cancer treatment; (6) (for cancer survivors with T2DM) current T2DM diagnosis as classified by a fasting blood glucose of ≥126 mg/dL, 2-hour oral glucose tolerance test of ≥200 mg/dL, HbA_1c_ level of ≥6.5%, or use of medications (eg, Metformin) or insulin to treat hyperglycemia or (for cancer survivors) no current T2DM diagnosis as classified by a fasting blood glucose <100 mg/dL, 2-hour oral glucose tolerance test <140 mg/dL, or HbA_1c_ level of <5.7%. Presence/absence of T2DM to be confirmed preferentially via physician’s documentation or via our measurement of participants’ fasting blood glucose during the blood draws within Part 2 of Baseline Testing (Figure 1); (7) own smartphone or computer with internet access; and (8) willing to participate in the 12-week remotely-delivered PA program. Our exclusion criteria are as follows: (1) reporting a Physical Activity Readiness Questionnaire score indicating PA may be unsafe unless a doctor’s note clearing a prospective participant for study participation can be provided; (2) engaging in ≥75 min/week of vigorous-intensity PA, ≥150 min/week of moderate-intensity PA, or an equivalent combination of both over the last 3 months; (3) currently undergoing active cancer treatment or planning more treatment within the next 3 months; (4) classified within the prediabetes range for their fasting blood glucose measurement (100-125 mg/dL) during Part 2 of Baseline Testing. Notably, those with T2DM verified via a physician’s documentation and who report the use of medications or insulin to treat hyperglycemia, who are found to be in the prediabetes range, will still be enrolled within the T2DM group and study. These results would indicate a participant with well-controlled T2DM, not prediabetes; and (5) currently a prisoner, pregnant, or planning to become pregnant during the study.

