##### Cerebrovascular and Cognitive Function as Well as Cardiometabolic, Proinflammatory, and Epigenetic Outcomes

Part 2 of Baseline and Poststudy Testing involves participants coming to one of the study laboratories (Oklahoma City, Oklahoma) following an 8-hour fast, 12 hours of caffeine abstinence, and 24 hours of no alcohol, vitamins, other health supplements, or nonsteroidal anti-inflammatory drug use. They may continue taking medications aligned with health conditions. Participants are also required not to have exercised intensely in the last 24 hours. During this session, participants first complete blood pressure measurements and then blood and saliva sample collections. Blood samples are being collected through traditional venipuncture of the antecubital vein by trained study personnel. Samples are immediately processed and stored at –80 °C. From these blood samples, we assess high- and low-density lipoprotein and total cholesterol, and fasting blood glucose, among other outcomes, using the Lipid Panel+ kit of Piccolo Xpress (Abbott, Chicago, Illinois). Further, we will use enzyme-linked immunosorbent assays to assess high-sensitivity C-reactive protein as well as interleukin-6 and monocyte chemoattractant protein 1—analyses to be run nearer the end of the study to ensure minimal batch effects. These data will allow us to measure cardiometabolic and proinflammatory cytokines aligned with CICI and T2DM pathophysiology [10,11,21]. Finally, we collect saliva with a DNA Genotek OMNIgene Saliva DNA and RNA collection kit (OMR-610; Ottawa, Ontario). Participants spit 1 mL of saliva into the collection tube to a marked fill line, snap the tube closed, and provide it to research staff, after which it is stored at –80 °C. For the purposes of this study, genomic DNA isolations will be performed from whole blood and saliva for epigenetic analyses, namely, DNA methylation. Similar to the enzyme-linked immunosorbent assays, epigenetic analyses will also take place nearer to the end of the study in order to randomize samples to minimize batch effects.

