### Statistical Analyses

We will first inspect all data for outliers/errors and normality, with analyses done in SPSS (version 29; IBM Corp) and R (R Foundation), depending on the metrics being analyzed. Baseline differences between cancer survivors with and without T2DM for (1) sociodemographics, (2) health characteristics, and (3) Aim 1/Exploratory outcomes (ie, cerebrovascular and cognitive function, cardiometabolic outcomes, proinflammatory cytokines, epigenome) will be compared using *t* tests or chi-square tests, as appropriate. Repeated measures ANOVA will analyze between-group differences for changes in Aim 1/Exploratory outcomes during the PA program (Aim 2) and Aim 3 outcomes (ie, SCT-related constructs, psychosocial outcomes, HRQoL, PA). If any sociodemographic or health characteristics differ at baseline between cancer survivors with and without T2DM, we will use repeated measures ANCOVA. Consistent with recommendations for pilot research [97,98], no a priori power analyses have been performed. Indeed, this study is designed to generate the data necessary to develop larger, properly powered, and federally funded studies on this critical topic.

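### Comparison participants are capped at a Part 2 fasting glucose below 100 mg/dL and that reading is also their Baseline value, so the between-group change in glucose is shifted toward T2DM by regression to the mean

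*Protocol article*

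**What the plan says.** Under Study Design and Recruitment, inclusion criterion 6 admits to the comparison group people with "no current T2DM diagnosis as classified by a fasting blood glucose <100 mg/dL", with an oral glucose tolerance test or HbA1c as alternatives. A fasting glucose of 126 mg/dL or more is one of the T2DM criteria. Presence or absence of T2DM is confirmed preferably by physician documentation, otherwise "via our measurement of participants’ fasting blood glucose during the blood draws within Part 2 of Baseline Testing". Exclusion criterion 4 then removes anyone "classified within the prediabetes range for their fasting blood glucose measurement (100-125 mg/dL) during Part 2 of Baseline Testing". The exception is for participants with documented T2DM who report glucose-lowering treatment and "who are found to be in the prediabetes range, will still be enrolled within the T2DM group and study".

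The measurement section describes one session held at both time points: "Part 2 of Baseline and Poststudy Testing involves participants coming to one of the study laboratories". From its blood samples "we assess high- and low-density lipoprotein and total cholesterol, and fasting blood glucose, among other outcomes".

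For the analysis, Statistical Analyses says: "Repeated measures ANOVA will analyze between-group differences for changes in Aim 1/Exploratory outcomes during the PA program (Aim 2"). ANCOVA is used only if sociodemographic or health characteristics differ at baseline. Specific Aim 2 predicts greater improvement in the T2DM group. The article describes no separate screening glucose and no repeat baseline draw.

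**The concern.** A single fasting glucose reading is a person's usual level plus day-to-day variation. If a group is kept only when that reading is below a ceiling, the kept readings are on average too low for the people who gave them, and the next reading rises with no real change. Here the ceiling binds every comparison participant: 100-125 mg/dL is excluded and 126 mg/dL or more meets a T2DM criterion. An HbA1c, a tolerance test or physician documentation may establish absence of T2DM, but exclusion criterion 4 still applies to the Part 2 reading.

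The T2DM group is not treated in the same way. Documented, treated participants face no cut, so their expected artificial change is about zero. Anyone admitted only because the Part 2 reading was 126 mg/dL or more is selected high and drifts down. Either way the group-by-time contrast on glucose does not have expectation zero when the program does nothing, and the error lies in the hypothesized direction. There is no untreated control group against which to measure the drift. A greater glucose improvement in T2DM could then be carried into planning of the larger trial when part of it came from the entry rule.

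**Working it through.** **What the article supplies.** The cut (below 100 mg/dL), the exemption, the shared draw, the contrast and the group sizes (15 and 15). It gives no mean, SD or test-retest reliability for glucose, so those are assumptions below, and there is no stated figure on this point to reproduce.

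**Comparator formula.** With mean μ and total SD σ before the cut, a = (100 − μ)/σ, and no true change:

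expected rise = (within-person variance / σ²) × σ × φ(a)/Φ(a).

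The first factor equals 1 − ρ, where ρ is the test-retest correlation.

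**Comparator results.**
- μ = 92, σ = 10, ρ = 0.75 (within-person SD 5): a = 0.8, φ/Φ = 0.368, rise = 0.25 × 10 × 0.368 = 0.92 mg/dL. The cut removes 21% of candidates.
- μ = 98, σ = 10, within-person SD 5.5: a = 0.2, φ/Φ = 0.675, mean of kept readings = 98 − 6.75 = 91.2, rise = 0.3025 × 6.75 = 2.04 mg/dL. The cut removes 42%.
- Over μ 88-96, σ 8-12, ρ 0.60-0.85: 0.17 to 2.87 mg/dL.
- Over μ 92-101, σ 10, within-person SD 4-7: 0.59 to 4.23 mg/dL. At the top end (μ = 101, within-person SD 7) the cut removes 54%.

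**Standardized size.** The test is between groups, so the SD of change is pooled. Comparators: 5.5 × √2 = 7.8. T2DM, assuming a within-person SD of 8 to 12: 11.3 to 17.0. Pooled over equal groups: √((7.8² + 11.3²)/2) = 9.7 to √((7.8² + 17.0²)/2) = 13.2. Hence 2.04 mg/dL is 0.15 to 0.21 SD, and 0.92 mg/dL is 0.07 to 0.10 SD.

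**T2DM side, only for those admitted on a reading of 126 mg/dL or more.** Expected fall = (within-person variance / σ²) × σ × φ(z)/(1 − Φ(z)), with z = (126 − μ)/σ. For μ 125-140, σ 30, within-person SD 8-12, this is 1.1 to 3.9 mg/dL. For μ = 140, σ = 35, ρ = 0.75, it is about 5 mg/dL.

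**Effect on the test.** With two time points, the group-by-time test amounts to a comparison of change scores. In 10,000 simulated trials with 15 per group and no true change (Welch t test; T2DM μ = 140, σ = 35, ρ = 0.75), the nominal rate of a significant result favoring T2DM is 2.5%. Simulated mean shift toward T2DM, with the rate of such results:

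| Comparators (μ, σ, ρ) | All T2DM exempt | All T2DM admitted on ≥126 |
|---|---|---|
| 88, 8, 0.85 | 0.2 mg/dL; 2.3% | 5.2 mg/dL; 11.5% |
| 92, 10, 0.75 | 0.9 mg/dL; 3.2% | 5.7 mg/dL; 12.5% |
| 96, 12, 0.60 | 3.0 mg/dL; 6.2% | 7.8 mg/dL; 19.4% |

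If instead no T2DM participant had the exemption and 100-125 mg/dL were removed from that group too, its artificial fall would be about 1.7 to 1.8 mg/dL.

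**The case against.** The strongest reply is that the effect is small and confined to one analyte. Much of this stands. The larger comparator shifts require 42% to 54% of candidates to fail the Part 2 cut, and nothing in the article points to failure rates that high. Status is checked in medical records whenever possible, so some candidates are filtered out beforehand. If all T2DM participants are documented and treated, the false-positive rate barely moves in the milder scenarios. The 12% to 19% rates assume that everyone in the T2DM group enters on the study's own reading, which the article makes the fallback route. It does not say how many, if any, will do so.

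It is also fair that this is an unpowered pilot, and that the limitations section concedes the lack of a control group. That does not answer the point: low power adds noise, whereas this is a directional error, and the stated limitations do not mention selection on the baseline reading. Nor does the ANCOVA provision help, because adjusting for sociodemographic or health characteristics leaves the truncation in place.

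A reader might infer that the entry rule favors T2DM across Aim 2. The text does not support that. Specific Aim 1, whose outcomes Aim 2 carries forward, names cerebrovascular measures, executive function, three inflammatory markers, blood pressure and insulin resistance. Only fasting glucose and an index computed from it share the truncated reading. A reader might also infer that comparison participants will visibly worsen. The shift is relative to their true change, and a real benefit could hide it.

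**Conclusion.** The point holds for fasting glucose and for any insulin-resistance index derived from the Part 2 reading. The entry rule, the shared draw and the between-group contrast of change together give a shift toward T2DM when there is no true change, and nothing in the article corrects it. The direction follows from the text, given that a Part 2 reading of 126 mg/dL or more keeps a person out of the comparison group. The size does not follow from the text: it rests on assumed means, SDs and reliability, normal readings, and within-person errors that are independent between visits.

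Under those assumptions the comparator rise is about 0.2 to 4 mg/dL, plausibly 1 to 2 mg/dL, or roughly 0.1 to 0.2 pooled SD of change. Dividing 2.04 by the comparators' own SD of change (7.8) gives 0.26, but that overstates the effect on a between-group test. The distortion becomes substantial only if many T2DM participants are admitted solely on a high Part 2 reading. This justifies changing the status of one contrast, not deleting it, and it does not undermine the other Aim 2 outcomes.

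**What to change.** Keep the analysis and make these changes to the wording in Statistical Analyses:

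- Label the between-group change in fasting glucose, and in any index derived from it, as descriptive and subject to regression to the mean from the entry rule. State that it will not be counted as support for the Aim 2 hypothesis.
- Report glucose change separately within T2DM participants whose status rests on physician documentation and treatment, since they are not selected on the Part 2 reading.
- Add a sensitivity analysis that subtracts the expected truncation shift, (1 − ρ) × σ × φ(a)/Φ(a), over a stated range of reliability, with the assumed mean and SD before the cut also stated.
- Report how many T2DM participants were admitted solely on a Part 2 reading of 126 mg/dL or more, because that number governs how large the shift can be.

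The cost is analysis wording, a short calculation, and one between-group contrast that loses inferential status. A separate eligibility reading before the Baseline draw would bring the expected artificial change to zero if within-person errors are independent. That would add a blood draw, and recruitment has been open since March 2025, so it could not help participants already measured.

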**Figure 1 figure1:**
[figure not shown]
Experimental design. HRQoL: health-related quality of life; NIH: National Institutes of Health; SCT: Social Cognitive Theory.

### Study Design

#### Overview

Figure 1 overviews our study design. While participants come to 2 separate laboratories during Baseline and Poststudy Testing Sessions Parts 2 and 3, given the nature of the assessments to be performed, the study is otherwise entirely remote, as shown on the right side of Figure 1. The left side of Figure 1 shows the approximate duration of each study component. We detail each aspect of the Baseline and Poststudy Testing Sessions noted within Figure 1 in the “Brief Aim-Specific Outcome Assessments” subsection. We detail the “12-Week Technology-based PA Program” noted within Figure 1 immediately below.

#### 12-Week Technology-Based PA Program

We are using a 12-week intervention strategy grounded in the SCT. Figure 2 outlines how this intervention aligns with the SCT’s reciprocally determinant constructs [58,59]: (1) personal cognitive factors; (2) environmental factors; and (3) supporting behavioral factors.

**Figure 2 figure2:**
[figure not shown]
Social Cognitive Theory-informed study components. HRQoL: health-related quality of life; PA: physical activity; RT: resistance training; SCT: Social Cognitive Theory.

We are using smartphone app (hereafter, “app”) technology to deliver our SCT-informed program. Via an Insight app developed specifically for this study (Figures 3A-3F), participants are receiving health-related educational messaging twice weekly in addition to continued access to information on the benefits of aerobic PA and RT for cancer survivors [63-65]. The health education messages are modeled after our prior studies [66-69]. These health education messages periodically request certain actions, such as setting “SMART Goals” and journaling, with the Insight app having locations where participants can continuously set and review their goals (Figure 3C) and journal entries (Figure 3D). These Insight app-delivered study components are targeting the SCT’s personal cognitive, environmental, and supporting behavioral factors. We developed this study-specific app as a research team and in collaboration with the Stephenson Cancer Center mHealth Shared Resource, which manages the Insight mHealth Platform [70]. While commercially available PA-oriented smartphone apps exist with some of these features, the content we are delivering to participants (enumerated above), as well as the delivery schedule for this content, is unique to our PA program—necessitating a customized app.

**Figure 3 figure3:**
[figure not shown]
Insight smartphone app. CICI: chemotherapy-induced cognitive impairment; PA: physical activity.

The MedBridge GO app (MedBridge Inc) (Figure 4A-E) is being used to deliver workout programs comprised of aerobic PA and RT to participants. We are implementing these workout programs via MedBridge GO, given the MedBridge GO app’s strong security measures and large exercise library (8000+ exercises) in addition to the platform’s ability to measure other items critical to the safe delivery of a PA program (eg, pain and difficulty scales for each prescribed exercise). Participants use MedBridge GO to select days each week on which they desire to complete workouts and set associated reminders (we recommend at least 2 workout sessions/week to all participants). Throughout Baseline Testing, we are collecting information about participants’ access to workout equipment, as well as their needs, constraints, and goals related to PA, via the study’s screening survey and a semistructured interview completed with the study’s exercise physiologist ([name]). All workouts delivered via MedBridge GO have instructions and associated videos to ensure proper form/safety, and participants use MedBridge GO to note if an exercise was too difficult or if they did not like the exercise. They can also communicate any further needs with the study’s exercise physiologist using MedBridge GO’s messaging feature. Thus, workouts are continuously tailored to each participant throughout study participation based on these different routes of communication. This communication engenders an element of supportive accountability [71] into this SCT-based, technology-delivered PA program. Briefly, the semistructured interviews regarding values and PA-related needs/constraints at Baseline and Midpoint (below), as well as regular communication with the study team via the MedBridge GO app, allow participants to develop a trusting, positive relationship with experts who prioritize their well-being [71]. To further increase the robustness of the PA program delivered via MedBridge GO, we are (1) providing resistance bands to each participant for incorporation into their workouts and (2) conducting another semi-structured interview at study midpoint—adjusting their PA programming for the second 6 weeks of the study in a manner that best meets each participant’s needs. The MedBridge GO workouts/training tutorials and exercise equipment package are targeting the SCT’s personal cognitive and environmental factors. Finally, participants are tracking their PA with the Fitbit Charge 6 during the study, provided during Baseline Testing Session Part 2, and complementing all other intervention components while facilitating self-regulatory behavioral skills. Improving skills, such as goal setting, related to the practice of a behavior, are notable SCT behavioral factors. We connect the Fitbit Charge 6 with Fitabase, a cloud-based platform for obtaining Fitbit/Garmin data [72].

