Aerobic physical activity (PA) and resistance training (RT) have robust health benefits counteracting much of the pathophysiology underlying CICI and T2DM [42,43]. Reviews [44,45] suggest better cerebrovascular function in those who are more active or fitter relative to those who are less active or fit, with greater fitness positively associated with cognitive function in other at-risk populations [46,47]. In those with T2DM, research has shown that PA is impactful at lowering proinflammatory cytokines [42,48-50] and improving insulin sensitivity [51,52]. Yet, research is needed on how increasing PA in cancer survivors with T2DM reporting CICI improves cerebrovascular and cognitive health through improved fitness. Notably, cancer survivors prefer supportive, individualized, home-based PA programming that includes RT and aerobic activities such as walking [53]. Home-based programs are recommended by the American Cancer Society [54] given their ability to circumvent some of the barriers to PA program participation (eg, distance to clinic, lack of time) among those living with and beyond cancer. Smartphone app technology can assist in providing this home-based PA program access. Relative to routine care, smartphone app–based supportive care among cancer survivors has been observed to improve HRQoL, self-efficacy, and symptoms of distress and depression [55]. Further, multicomponent interventions that include personalized PA programming delivered via smartphone apps, with wearable devices to supplement behavior change, have shown promise for increasing PA among cancer survivors [56,57].

We are conducting a 30-participant pilot study in cancer survivors with T2DM (n=15) and without T2DM (n=15)—all self-reporting “chemo-brain”—that includes personalized PA programming and education delivered via 2 smartphone apps, with a wearable device provided for further behavior change support. We have detailed our Specific Aims and Hypotheses below.

### Specific Aim 1

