##### SCT-related Construct, Psychosocial, HRQoL, and PA Outcomes

We are measuring all Aim 3 outcomes during Part 1 of participants’ Baseline and Poststudy Testing Sessions, as well as during Midpoint Testing. The exception is PA, which is only measured at Baseline and after the 12th study week. We are assessing SCT-related psychosocial outcomes using validated surveys delivered via REDCap. Self-efficacy is being assessed using a 9-item measure from Rodgers et al [82]. Participants are noting their confidence during different PA-related situations (“0%: Not confident at all” to “100%: Extremely confident”; 10% increments). Social support is being evaluated using the Social Support and Exercise Survey, with participants reporting frequency of PA support over the last 3 months from family and, separately, friends (“1: None” to “5: Very often”) [83]. PA-related enjoyment is being measured via the 18-item Physical Activity Enjoyment Scale [84], with feelings related to PA-related statements/situations reported on a 7-point scale (varied response options). We are using a 14-item scale [85] to assess agreement between hypothetical PA barriers and participants’ perceived barriers (“1: Strongly disagree” to “4: Strongly agree”). Last, we are using the 13-item Outcome Expectations for Exercise Scale-2 [86] to assess agreement with listed positive and negative benefits of PA (“1: strongly agree” to “5: strongly disagree”).

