We are assessing stress, anxiety, mood, and depressive symptoms and HRQoL using validated instruments. We are measuring chronic stress with the 10-item Cohen Perceived Stress Scale [87]. Participants report stress frequency over the last month (“0: Never” to “4: Very often”). We measure chronic anxiety with the State-Trait Anxiety Inventory [88,89], which includes 20 items, each on state and trait anxiety (“1: Almost never” to “4: Almost always”). Chronic mood is being assessed by the Positive and Negative Affect Scale [90]. This scale has 10 items, each for positive and negative affect (“1: Very slightly or not at all” to “5: Extremely”). Chronic depressive symptoms are being assessed by the 9-item Patient Health Questionnaire-9 [91] (“0: Not at all” to “3: Nearly every day”). For HRQoL, the following components of physical and psychological health are being assessed using the Patient-Reported Outcomes Measurement Information System: physical functioning, fatigue, anxiety, depression, pain interference, pain intensity, sleep impairment, and sleep disturbance [92,93]. Measurements are on a 5-point scale, with 5 being the worst on all components aside from physical function, where higher scores are better.

We are assessing PA between Baseline Testing Session Parts 2 and 3 and just after the 12th study week with ActiGraph wGT3X-BT accelerometers—valid for free-living PA assessments [94]. Established protocols for placement and wear duration are being followed by participants [95], and accepted thresholds (≥10 hours/day of wear time; at least 4 days, including one weekend day) are used to clean these data. Established cut points will be used to analyze PA durations per day [96]. Daily average minutes of moderate-to-vigorous PA, light PA, and sedentary behavior will be reported.

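### The Fitbit, an intervention component, is handed out before baseline accelerometry, and nothing shown says it stays inactive until that baseline is complete

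*Protocol article*

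**What the plan says.** Under Methods, 12-Week Technology-Based PA Program, the protocol article states that "participants are tracking their PA with the Fitbit Charge 6 during the study, provided during Baseline Testing Session Part 2". The same sentence gives the device an intervention role: it is "complementing all other intervention components while facilitating self-regulatory behavioral skills". The Background section describes the program likewise, "with a wearable device provided for further behavior change support".

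Under SCT-related Construct, Psychosocial, HRQoL, and PA Outcomes, the timing of the outcome measurement is: "We are assessing PA between Baseline Testing Session Parts 2 and 3 and just after the 12th study week with ActiGraph wGT3X-BT accelerometers". A usable record needs at least 10 hours of wear per day on "at least 4 days, including one weekend day". PA is not part of Midpoint Testing: "The exception is PA, which is only measured at Baseline and after the 12th study week".

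The outcome feeds Specific Aim 3, part 4, which expects the T2DM group to improve more in "overall PA participation due to greater increases in light and moderate PA".

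**The concern.** A pre-program value should describe behavior before any part of the program acts on it. By the article's own theory, a wearable that shows people their activity supports self-regulation and so is meant to change activity. Yet the device is issued at the session that opens the window for baseline accelerometry, and that window must span several days to yield a valid record.

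If participants use the Fitbit in that window, baseline PA already contains part of the intervention effect. The pre-to-post change would then understate what the full program did. There is no control group and no other accelerometer measurement before the program, so nothing in the design would reveal this. The study exists to inform a larger trial, so an understated PA change could carry into that trial's planning.

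**Working it through.** **Plan's own figure.** The only sample-size figure is the accrual target: "Our accrual target is 38 participants to allow our desired number of 30 participants to be achieved when accounting for an anticipated 20% attrition rate". It reproduces: 30 / (1 − 0.20) = 37.5, rounded up to 38. The point does not depend on it, but it shows how small the sample is that any sensitivity analysis would divide.

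**Order of events, from the text.**

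1. Baseline Part 2 (Oklahoma City laboratory): the Fitbit is provided.
2. Between Parts 2 and 3: baseline ActiGraph wear, at least 4 valid days.
3. Baseline Part 3 (Norman laboratory): transcranial doppler and exercise testing.
4. Twelve-week program.
5. Just after week 12: second and last ActiGraph wear.

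Step 1 comes before step 2. No shown text says the device is masked, unpaired or unworn during step 2. Nor does any shown text say that it is switched on at step 1. The text gives a hand-out time and says tracking takes place during the study.

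**Effect on the within-group change.** Let B be a participant's mean daily PA without any intervention component, g the true gain by the end of the program, and r the increase caused by Fitbit use during baseline wear.

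- Recorded at baseline: B + r
- Recorded after week 12: B + g
- Observed change: (B + g) − (B + r) = g − r

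The bias is −r. It is toward zero when r lies between 0 and g. If the device is inactive during baseline wear, r = 0 and there is no bias.

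**Effect on the between-group contrast.** Under Statistical Analyses, repeated-measures ANOVA (or ANCOVA) compares changes between groups. With subscript 1 for T2DM and 0 for no T2DM:

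- Observed difference in change: (g1 − r1) − (g0 − r0) = (g1 − g0) − (r1 − r0)

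If r1 = r0, the bias cancels. It remains only to the extent that r differs between groups.

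**Illustration only.** The documents give neither r nor g. With assumed values in minutes per day:

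| Assumed true gain g | Assumed r | Observed g − r | Share of g observed |
|---|---|---|---|
| 10 | 0 | 10 | 100% |
| 10 | 2 | 8 | 80% |
| 10 | 5 | 5 | 50% |
| 20 | 0 | 20 | 100% |
| 20 | 2 | 18 | 90% |
| 20 | 5 | 15 | 75% |

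The table shows the mechanism. Its spread comes entirely from the assumptions, so it is not an estimate for this trial.

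**The case against.** The strongest reply is that handing out a device is not the same as switching it on. The sentence about the Fitbit sits in the description of the 12-week program, and the article elsewhere uses study midpoint and study week for the program period, so tracking that starts with the program is a plausible reading. Figure 1, which sets out the sequence, is not shown, and the full protocol is available only on request. Either could hold an activation instruction. This stands: a reader might infer that contamination is established, but the text supports only the conditional statement.

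A reader might also infer that the planned group comparison is biased. The text does not support that either. A response common to both groups cancels, and the hypothesis that the T2DM group will increase PA more does not show that this group reacts more to the device in the baseline days.

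It can further be said that the within-group change is already hard to attribute to the program, because the article concedes the lack of a true control group. That limits what the change can show, but it does not justify an additional bias that can be avoided.

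Finally, a change during recruitment creates two baseline conditions in a sample of at most 38. That is a real cost, and the fix has to deal with it openly.

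**Conclusion.** The point holds in conditional form. As written, the sequence puts an intervention component in participants' hands before the only pre-program PA measurement, and no shown text keeps it inactive. If it is in use during baseline wear, the within-group PA change in Aim 3, part 4 is biased toward zero, provided the device raises activity by less than the program's full gain. The size cannot be estimated from the documents, and no percentage should be attached to it. The group difference in change is affected only if the response differs by T2DM status, for which the documents give no evidence.

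It would also be too strong to say that nothing can be done for participants already enrolled. An unaffected baseline cannot be re-measured, but Fitbit use during baseline wear may be identifiable, and its influence on the result can then be examined.

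Severity is moderate. One outcome of Aim 3 is concerned, in a pilot for which no power analysis was made. The cerebrovascular, cognitive, inflammatory and psychosocial outcomes do not use the ActiGraph record.

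**What to change.** 1. State in the protocol and the visit checklist that the Fitbit is either handed out only once baseline ActiGraph wear is complete (at Part 3 or program start), or given at Part 2 but left unpaired and unworn until then. If this is already the practice, one clarifying sentence settles the point.
2. For participants already enrolled, use the Fitabase records to flag whether the Fitbit was in use during the baseline ActiGraph days, and report the number flagged in each group.
3. Keep every participant in the main PA analysis. Report the PA change with and without the flagged participants as a sensitivity analysis. With few per group, this will be descriptive.
4. State in the report that baseline conditions changed during recruitment and from what date. Flagged status will largely follow enrollment date, so a difference between the two sets of results cannot be put down to the device alone.

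Cost: a short protocol change and an IRB modification, with no extra visit because Part 3 is already in person. Parts 2 and 3 are at different laboratories, so moving the hand-out may move device set-up between sites; delayed activation avoids that. Recruitment is expected to run until late 2026, so acting soon limits the number of affected baselines.
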